## 2 Materials and methods

### 2.1 Study design

This experimental pre-post study is designed to investigate the acute effect of diaphragmatic breathing exercises on recovery of fatigue-induced changes in spinal mobility and postural stability in sedentary middle-aged adults at risk of developing non-specific low back pain. This is a study protocol that will be carried out and reported in accordance with the Standard Protocol Items: Recommendations for Interventional Trials statement (SPIRIT). Figure 1 illustrates the study design. The study has been approved by the ethics committee of the Faculty of Physical Education and Sport, Comenius University in Bratislava (No. 5/2022) and the Ethics Committee of Kerman University of Medical Sciences (IR.KMU.REC.1401.386). It also has been approved by Iranian Registry of Clinical Trials (registration reference: IRCT20221126056606N1).

**FIGURE 1 F1:**
[figure not shown]
Flow-diagram of the study protocol.

### 2.2 Participants and setting

This study will be performed on 20 sedentary individuals aged 25–44 years old, at risk of developing non-specific low back pain, who will mainly be employees of university. This effect size is sufficient to determine the significant effects of diaphragmatic breathing exercises on the recovery of spinal mobility and postural stability due to trunk muscles fatigue.

The present study will be performed at the Faculty of Physical Education and Sport, Comenius University in Bratislava, Slovakia.

#### 2.2.1 Inclusion and exclusion criteria

Inclusion criteria for the participants were established as follows: The sedentary middle-aged adults (aged 25–44 years old) at a risk of developing non-specific low back pain, and self-reporting of sitting for at least 2 hours on any working day (Saiklang et al., 2022). Potential participants will be screened for the study using the international physical activity questionnaire (IPAQ) to recognize those who are sedentary and using the Acute LBP Screening Questionnaire (ALBPSQ) to identify those who are at risk of developing non-specific low back pain. The volunteers will be excluded if they meet any of the following criteria: pregnancy (Abboud et al., 2014); history of spinal, femoral, or intra-abdominal surgery in the previous 12 months (Sitthipornvorakul et al., 2015); have been diagnosed with a congenital anomaly of the spine, arthritis, rheumatoid, infection of the spine and discs, spondylolisthesis, ankylosing spondylitis, spondylosis, tumor, systemic lupus erythematosus, or osteoporosis (Sitthipornvorakul et al., 2015); receiving physiotherapy services 1 month before the beginning of the study (Fortun-Rabadan et al., 2021); having suffered any kind of mental health disorder, including anxiety and depression, during the past 3 years (Fortun-Rabadan et al., 2021).

#### 2.2.2 Sample size estimation and sampling method

A prior sample size estimation was done using the G*Power software package (version 3.1.9.7) based on the study by Fonta et al. (2021). The input parameters were as follows: statistical test = repeated measures, within - between interaction; effect size F = 0.25; α err prob = 0.05; and power (1 − β err prob) = 0.80. As a result, the total sample size was calculated to be 11 subjects. In consideration of the possibility of dropouts, a slightly larger number of subjects will be recruited to participate in this study. The total sample size would be approximately 20 subjects.

A purposeful sampling strategy will be used and participants based on their age, sedentary behavior, and other relevant factors that are related to the study’s focus and have been explained in inclusion and exclusion criteria section will be selected.

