### 2.4 Statistical analysis

Statistical analyses will be carried out using SPSS Statistics (SPSS Statistics Version 24; IBM Corporation^©^, United States). Prior to statistical comparisons, a Shapiro-Wilk test of normality will be performed for all variables. Not normally distributed data will be analyzed using nonparametric tests. Friedman’s test followed by Dunn’s *post hoc* test will be used for the comparison of the spinal mobility, postural stability and EMG variables at different assessment times (at baseline, immediately after Abt’s fatigue protocol, immediately after recovery modalities, 15-min after recovery modalities, 30-min after recovery modalities). The Kruskal–Walli’s test will be used for the inter-group comparisons (experimental group A vs. experimental group B) at each assessment. For the normally distributed data, a repeated measures Analysis of Variance (ANOVA) will be performed. Repeated measures ANOVA will be used to confirm if there are differences in each group (within-group comparisons), considering each group in isolation, between the five assessments in each of the spinal mobility variables (at baseline, immediately after Abt’s fatigue protocol, immediately after recovery modalities, 15-min after recovery modalities, 30-min after recovery modalities). To calculate between-group differences from baseline assessment to final follow up, a five-way repeated-measures ANOVA will be performed. With the spinal mobility and/or postural stability and/or EMG variables outcome as dependent factor, with five levels corresponding to every time of assessment (t1, t2, t3, t4, and t5), and the two groups (experimental group A vs. experimental group B) as independent factors. The Bonferroni correction will be applied to control for the increased probability of significant findings due to multiple testing. Between- and within-group effect sizes for all quantitative variables will be measured with the Cohen d coefficient: small effect (less than d = 0.2 and ηp2 = 0.01); moderate effect (approximately d = 0.5 and ηp2 = 0.06); and large effect (greater than d = 0.8 and ηp2 = 0.14) (Cohen, 2013). The α-level will be set to 0.05 for all statistical tests.

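### The sample size of 11 is calculated for independent groups although each participant receives both recovery modalities, and it cannot be verified from the inputs listed, so the planned 20 has no documented basis

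*Protocol article*

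**What the plan says.** Section 2.2.2 gives the G*Power inputs as "statistical test = repeated measures, within - between interaction; effect size F = 0.25", with "α err prob = 0.05" and power 0.80, based on one cited study from which no figures are given. It then states: "As a result, the total sample size was calculated to be 11 subjects". The number of groups, the number of measurements, the correlation among measurements and the sphericity value are not listed. To allow for dropout, for which no rate is given, the total is raised to approximately 20.

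Section 2.2 relies on that number: "This effect size is sufficient to determine the significant effects of diaphragmatic breathing exercises on the recovery of spinal mobility and postural stability". The figure referred to there is the 20 participants, which is a sample size and not an effect size.

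The abstract describes twenty adults who each go through the fatigue protocol followed by breathing exercises and by passive rest, with a week in between. Section 2.3.2 lists four assessments for each modality: baseline, after fatigue, immediately after recovery and 15 minutes after recovery. Section 2.4 adds a fifth at 30 minutes and fits a repeated-measures ANOVA with "the two groups (experimental group A vs. experimental group B) as independent factors".

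**The concern.** In a within-between interaction, the between part is a factor that separates different people. In the abstract's design nothing does: modality, like time, varies within each person. Sections 2.2.2 and 2.4 agree with each other, but both treat as independent groups what the abstract describes as one cohort.

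This matters for two reasons. First, the 80% power is the only quantitative support for the claim in section 2.2 that the number is sufficient, and it is not the power of the comparison that the hypothesis concerns (active versus passive recovery within the same person). Second, the inputs that decide the answer are not given, so a reader cannot tell what effect the trial could detect or how to read a non-significant result. The step from 11 to 20 is presented as a slight increase, yet 20/11 = 1.82. That is 82% more participants, enough to absorb a loss of 9 out of 20, or 45%.

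**Working it through.** **Inputs from the documents.** f = 0.25, alpha = 0.05, power = 0.80, stated total 11 (section 2.2.2); two groups, k = 2, and five assessments, m = 5 (section 2.4); four assessments, m = 4 (section 2.3.2); planned total 20 (sections 2.2 and 2.2.2).

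**Assumptions, because the article gives no value.** Correlation among repeated measurements rho = 0.5, varied below; sphericity epsilon = 1; one common correlation.

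**Step 1: try to reproduce 11 with the named test.** Noncentral F with lambda = f² × N × m / (1 − rho), df1 = (k − 1)(m − 1), df2 = (N − k)(m − 1).

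For N = 11, m = 5, rho = 0.5: lambda = 0.0625 × 11 × 5 / 0.5 = 6.875, df = 4 and 36, power 0.47. For m = 4: lambda = 0.0625 × 11 × 4 / 0.5 = 5.5, df = 3 and 27, power 0.42.

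| Named test, k = 2, epsilon = 1 | m = 5 | m = 4 |
|---|---|---|
| Total N for 80% power, rho = 0.5 | 22 (21 if groups may be unequal) | 24 |
| Power at N = 11, rho = 0.5 | 0.47 | 0.42 |
| Power at N = 20, rho = 0.5 | 0.79 | 0.73 |
| Power at N = 20, rho = 0.3 | 0.63 | 0.57 |
| rho at which N = 11 gives 80% | about 0.75 | about 0.78 |

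A total of 11 is therefore not reproduced at rho = 0.5. It is reached only at a considerably higher correlation, which the article does not state.

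**Step 2: the same effect size in the design that the abstract describes.** With modality and time both within person, the interaction has lambda = f² × N × 2m / (1 − rho), df1 = m − 1, df2 = (N − 1)(m − 1). This assumes that f = 0.25 applies to that interaction.

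For N = 11, m = 5, rho = 0.5: lambda = 0.0625 × 11 × 10 / 0.5 = 13.75, df = 4 and 40, power 0.81. For m = 4: lambda = 0.0625 × 11 × 8 / 0.5 = 11.0, df = 3 and 30, power 0.745.

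| Within-person interaction, epsilon = 1 | m = 5 | m = 4 |
|---|---|---|
| N for 80% power, rho = 0.5 | 11 | 13 |
| Power at N = 20, rho = 0.5 | 0.98 | 0.97 |
| Power at N = 20, rho = 0 | 0.79 | 0.73 |

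At m = 5 and rho = 0.5, epsilon = 0.75 raises the required N from 11 to 13, and epsilon = 0.5 raises it to 17.

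**Step 3: a single active-versus-passive contrast.** Paired t test, two-sided 0.05 without adjustment, noncentrality dz × √n, n − 1 degrees of freedom. The paired standardised difference dz detectable with 80% power is:

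| Completers | dz |
|---|---|
| 20 | 0.66 |
| 18 | 0.70 |
| 16 (20% loss from 20) | 0.75 |
| 11 | 0.94 |

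**The case against.** Four points can be made for the plan.

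- *The test named is the test planned.* Section 2.4 does specify a group A versus group B repeated-measures ANOVA, so it would be wrong to say that the calculation belongs to an analysis the trial does not run. This stands. The conflict is between the design in the abstract on one side and sections 2.2.2 and 2.4 together on the other.
- *Eleven is attainable.* A reader might infer from Step 1 that 11 is impossible or an arithmetical error. The documents do not support that. The listed inputs fix no single N, the cited study may have supplied a correlation near 0.75, and an article may leave secondary software settings to the full protocol. Eleven is also half of 22, and it is exactly the within-person answer for five assessments at rho = 0.5. None of this repairs the text. A per-group 11 would contradict the word total, the within-person model is not the test named, and with the four assessments collected it needs 13.
- *The trial plans 20, not 11.* A reader might infer that the trial is underpowered. That is not shown. On the within-person model at rho = 0.5, 20 gives 0.97 to 0.98, and even the named test gives 0.79 with five assessments. The adequacy of 20 depends on values that the article does not state.
- *A single paired contrast is not the planned analysis either.* Section 2.4 plans several assessments with a Bonferroni correction, and section 2.3.2 labels only the screening questionnaires primary and the intervention measures secondary. This stands, and the fix allows for it.

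**Conclusion.** The point holds in this form. The sample size calculation and the analysis model both assume independent groups, while the abstract describes one cohort receiving both modalities. The 80% power at 11 is therefore attached to a model that the design does not have. The conflict itself depends on no assumption; it follows from setting the abstract beside sections 2.2.2 and 2.4.

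The figure of 11 also cannot be verified. With k = 2, epsilon = 1 and rho = 0.5, the named test needs twice that number or slightly more (22 or 24). These totals rest on the assumed correlation, and the listed inputs do not rule out a higher one.

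The claim in section 2.2 that the number is sufficient is accordingly unsupported. The defect lies in the documentation of 20 and not in a demonstrated shortage of participants.

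**What to change.** 1. In section 2.2.2, remove the within-between calculation and the figure of 11. Keep 20.
2. State what 20 delivers for the within-person comparison of active with passive recovery. Either give a paired contrast (80% power at unadjusted two-sided 0.05 for a standardised difference of 0.66 with 20 completers, or 0.75 with 16), or give a modality-by-time interaction with both factors within person, stating the number of assessments, the correlation, epsilon and the source of the effect size.
3. Name the outcome variable to which the calculation applies and the assumed dropout rate. Settle whether there are four or five assessments, since sections 2.3.2 and 2.4 differ.
4. In section 2.4, replace the independent-groups model with one in which modality is a within-person factor. Say how the Bonferroni correction changes the power figure; any division of alpha raises the detectable difference above the unadjusted values given here.
5. In section 2.2, replace the sentence that calls the number of participants a sufficient effect size with the statement from item 2.

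The cost is text only. No participants are added. The stated sensitivity may look less favourable than 80% power at 11, but it will describe the trial as designed.

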### 2.3 Procedures

Each participant will take part in two phases of the experiment including familiarization and data collection.

#### 2.3.1 Familiarization

In the first phase, all subjects will undergo a familiarization session, about 1–2 h before data collection. The study objectives and procedures will be explained to participants and informed consent will be taken from each participant before the study. In the second phase, participants will complete a questionnaire that includes personal and baseline characteristics. Body mass will be measured using a calibrated digital scale, and height will be measured using a single stadiometer. The weight plates used in the trunk muscles fatigue protocol for each participant will be chosen during the familiarization phase. The heaviest weight that participants can perform each exercise 20 times in 40 s in the correct form will be used (Askari and Esmaeili, 2021). During this phase, subjects will be asked to eat their normal meal while avoiding strenuous exercise and performance-enhancing energy drinks for the 48 h prior to data collection sessions (Armstrong et al., 2018).

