#### 2.3.2 Data collection

Data from all participants will be collected under three conditions:1. Pre-fatigue assessment (at baseline),2. Post-fatigue assessment (immediately after fatigue protocol),3. Post-recovery modalities assessment (immediately, and 15-min after cessation of active and passive modality, respectively).

Assessing the effects of the intervention at the 15-min follow-up can provide insight into the potential duration of these effects.

All participants will be tested at the same time of day by the same examiners.

The study will involve gathering individual demographic information and outcome data. The study team will enter the questionnaire data into a database and verify its accuracy before using it. All information and outcome data will be kept on password-protected computers that only the authorized members of the study team will be able to access. Data management will outline the procedures for gathering, recording, storing, and archiving data.

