###### 2.3.2.2.2 Assessment of the spinal mobility

Intersegmental mobility, overall and regional spinal range of motion will be measured in the sagittal plane in the standing position using a Spinal Mouse device (Csuhai et al., 2020). It is a wireless electronic, and non-invasive skin-surface tool for computer-assisted imaging and radiation-free examination (Post and Leferink, 2004). The Spinal Mouse’s reliability and validity have been established in populations that were healthy and symptomatic, including back pain (Topalidou et al., 2014). Before starting the examination, every subject will be registered in Spinal Mouse software with gender, age and randomly allocated study codes. Subjects will be asked to take three different standing positions: relaxed but erect (not corrected), maximal flexion and maximal extension of the spine. After undressing the upper body, spinous processes will be palpated, and C7 and S3 will be marked with a body-marker. Spinal Mouse will run paravertebrally along the spinous processes of marked segments. It makes the system capable of recording the contour of skin above the vertebral bodies in the sagittal plane. Positions include:1. Neutral in standing: Subject will be asked to maintain a relaxed position with the feet shoulder width apart, with straight knees and arms by the side, looking and facing straight horizontally towards the wall.2. Maximal flexion in standing: Subject will be asked to flex the trunk with straight knees as far as possible with slow motion from segment to segment, aiming to touch the ground with fingertips.3. Maximal extension in standing: Subject will be asked to cross arms in front of the chest and extend the trunk as far as possible, keeping the knees straight, without extension of the cervical spine.

No warm-up will be performed before the examination and each test will be done once (Post and Leferink, 2004). The mobility values of the segments, including range of flexion from upright (U-F), range of extension from upright (U-E) and total range from extension to flexion (E-F), will be measured (Csuhai et al., 2020).

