###### 2.3.3.2.3 Assessment of the postural stability

Participants will be asked to stand barefoot on a force plate with their arms relaxed comfortably at their sides. They will be instructed to stand in an upright position with their feet abducted at 10° and their heels separated mediolaterally by a distance of 6 cm. A series of trials will be conducted in a randomized order under varied conditions: tandem stance on a force plate with eyes open, tandem stance on a force plate with eyes closed, tandem stance on a foam mat (Airex Balance Pad) placed on the force plate with eyes open, tandem stance on a foam mat (Airex Balance Pad) placed on the force plate with eyes closed (Zemková et al., 2016). Subjects will perform one set of 30s under each condition. Short rest periods break will be allowed after every two trials (Zemková et al., 2021c).

Postural stability will be assessed using a FiTRO Sway Check (FiTRONiC, Bratislava, Slovakia). The system measures the actual force in the corners of the force plate and calculates an instant position of the CoP (sampling rate: 100Hz, 12-bit AD signal conversion, resolution of the CoP position: less than 0.1mm, measuring range: 0–1,000/s, non-linearity: ±0.02%FS, combined error: 0.03%, sensitivity: 2 mV/V ± 0.25%, overload capacity: 150%/sensor). FiTRO Sway Check has been shown to have good to excellent reliability of CoP variables, according to a recent study by Zemkova et al. (2021) (Zemková et al., 2021c). The Romberg quotient (eyes closed/eyes open (EC/EO) sway ratio) will also be calculated. Under unstable conditions, variables of postural stability will be registered by using the FiTRO Sway Check (FiTRONiC, Bratislava, Slovakia). The device consists of a square platform supported by four springs with an elasticity coefficient of 40N/mm. Shifting the CoP in the horizontal plane leads to changes of body weight distribution to the four corners of the platform. Force acting in each corner is calculated as a product of the coefficient of elasticity of the spring used and vertical distance measured by means of a fine sensor. The analogue signals are AD-converted and sampled by computer at the rate of 100Hz. Calculations of instant CoP position is based on force distribution to the four corners of the platform. Basic parameters of postural stability (i.e., mean CoP velocity and mean CoP displacements in medio-lateral and anterior-posterior directions) will be analyzed (Zemková et al., 2021c).

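### No practice of the balance or mobility tests is described, so practice gain, mainly at visit 1, may mask fatigue and inflate apparent recovery

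*Protocol article*

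**What the plan says.** **Familiarization (section 2.3.1).** The protocol states that "all subjects will undergo a familiarization session, about 1–2 h before data collection". The content is then itemised. "The study objectives and procedures will be explained to participants and informed consent will be taken from each participant before the study". A questionnaire, body mass and height follow, and then the loads: "The weight plates used in the trunk muscles fatigue protocol for each participant will be chosen during the familiarization phase". Instructions on meals, exercise and energy drinks complete the list. The only physical rehearsal is of the fatiguing exercises.

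**Balance tests (section 2.3.3.2.3).** There are four tandem-stance conditions: firm or foam surface, eyes open or closed. "Subjects will perform one set of 30s under each condition". On order: "A series of trials will be conducted in a randomized order under varied conditions".

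**Mobility tests (section 2.3.2.2.2).** There are three standing positions. "No warm-up will be performed before the examination and each test will be done once".

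**Repetition.** Section 2.3.2 gives four assessments per visit: baseline, post-fatigue, immediately after recovery, and 15 minutes later. Section 2.4 gives five, with the post-recovery times listed as "immediately after recovery modalities, 15-min after recovery modalities, 30-min after recovery modalities".

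**Order of modalities.** The abstract has the same twenty people do active recovery as item 1 and passive recovery as item 2, one week apart. No section states a randomised or counterbalanced order.

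**Analysis (section 2.4).** Time is tested within each condition separately. The two conditions are also compared over time.

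**The concern.** Tandem stance on foam with eyes closed is an unfamiliar task, and people may improve on it over the first few attempts. The time points always run in the same sequence: baseline, post-fatigue, post-recovery. A gain from repetition therefore works against the fatigue effect (baseline to post-fatigue) and adds to the recovery effect (post-fatigue to later).

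Both conditions include the fatigue protocol, so no series of repeated tests without fatigue exists from which learning could be estimated and subtracted. Randomising the four stance conditions balances order between those conditions and leaves the time points unbalanced. At stake is whether a within-condition change can be read as fatigue or recovery. If the modality order is fixed, there may also be a small advantage for the modality tested first.

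**Working it through.** **1. What the text fixes.** Section 2.3.1 names each element of the session, down to the scale and stadiometer, and names no outcome test. Sections 2.3.2.2.2 and 2.3.3.2.3 describe the tests in detail, set one trial each, and mention no practice trial. Followed as written, the first balance or mobility test a participant does is the visit 1 baseline. By visit 2 the participant has done each test four or five times.

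**2. The shape of learning matters.** If performance improved by the same proportion at every attempt, an extra trial before baseline would rescale all later values alike, and the ratio of post-fatigue to baseline would not change. A practice trial helps only if early gains are larger than later ones. The illustration therefore uses a front-loaded curve.

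**3. Illustration (all inputs assumed; the documents give none).** Let the gain after k earlier attempts be P(k) = T(1 − q^k). T is the total possible gain in SD units, 0.1 to 0.5, and q is 0.5 or 0.7. Take four assessments per visit and no forgetting over the week. Visit 1 is then k = 0 to 3 and visit 2 is k = 4 to 7.

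- Visit 1, baseline to post-fatigue (masks fatigue): T(1 − q)
- Visit 1, post-fatigue to post-recovery (looks like recovery): Tq(1 − q)
- Visit 2, post-fatigue to post-recovery: Tq^5(1 − q)
- Bias in the active–passive recovery contrast if active is always first: the second minus the third

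| T | q | Masks fatigue, visit 1 | False recovery, visit 1 | False recovery, visit 2 | Bias, fixed order |
|---|---|---|---|---|---|
| 0.1 | 0.5 | 0.050 | 0.025 | 0.002 | 0.023 |
| 0.1 | 0.7 | 0.030 | 0.021 | 0.005 | 0.016 |
| 0.5 | 0.5 | 0.250 | 0.125 | 0.008 | 0.117 |
| 0.5 | 0.7 | 0.150 | 0.105 | 0.025 | 0.080 |

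For example, with T = 0.5 and q = 0.5: 0.5 × 0.5 = 0.250; 0.5 × 0.5 × 0.5 = 0.125; 0.5 × 0.03125 × 0.5 = 0.008; 0.125 − 0.008 = 0.117.

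**4. Effect of one practice trial.** Every k rises by one, so every entry is multiplied by q. The visit 1 masking of fatigue falls from 0.030–0.250 to 0.021–0.125 SD (0.030 × 0.7 and 0.250 × 0.5). The practice effect is cut by 50% (q = 0.5) or 30% (q = 0.7) and is not removed.

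**5. The comparison of modalities.** Both modalities repeat the same test series. With balanced order, the visit 1 and visit 2 gains average out across modalities. With active always first, the last column applies.

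**The case against.** **The point rests on silence in a condensed article.** This is fair in part. A reader might infer that the protocol excludes practice. It does not: no practice is described, and none is ruled out. What remains is that the session is itemised and the tests are fixed at one trial each, so a site following this text would not rehearse them. If practice is already planned, one sentence settles the matter.

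**The hypothesis is comparative.** This stands. Active is to be compared with passive recovery, and a gain common to both largely cancels. A reader might infer that the main comparison is invalid, and the documents do not support that. The remaining route is the order: the abstract reads as active then passive, and no balancing is stated. The flow diagram (Figure 1) could not be read here. If it shows a balanced order, or if groups A and B in section 2.4 are two sequences or separate sets of people, that part falls away.

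**Only the visit 1 baseline can be a first attempt.** This stands and limits the point.

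**Fatigue is not judged from sway alone.** This stands. EMG (section 2.3.2.2.1) and a Borg rating of 17 or more (section 2.3.3) bear on whether fatigue occurred. They do not show how much sway or mobility changed because of it.

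**Mobility is a weaker case.** This also stands. One of the three positions is relaxed standing, which offers little to learn. Section 2.3.3 also puts a 10-minute warm-up with hamstring and trunk stretching before the fatiguing exercises, and so between the baseline and post-fatigue mobility tests. That is a separate confounder.

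**Conclusion.** The point holds as a cheap improvement to the design; it does not show an error in the plan's figures. As written, the visit 1 baseline is unpractised. If learning is front-loaded, the within-condition tests in section 2.4 may understate fatigue and overstate recovery, mainly at visit 1 and mainly for tandem-stance sway.

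The direction follows from the test sequence; the size is unknown. Under the assumed curve, practice at visit 1 masks 0.03 to 0.25 SD of fatigue and adds 0.02 to 0.13 SD of apparent recovery. If SD is read on the scale of d, the upper masking figure is half of the 0.5 that section 2.4 calls moderate, and the lower figures are negligible. The active–passive contrast is affected only if active recovery always comes first, by about 0.02 to 0.12 SD in its favour.

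A reader might go further and conclude that practice hides most of the fatigue effect or accounts for the recovery. The documents contain no practice rate from which to claim that.

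**What to change.** Add to section 2.3.1 one unrecorded practice trial of each of the four balance conditions and one practice set of the three Spinal Mouse positions. Do not place them directly before baseline. Leave the breathing technique out of this practice, so that the passive condition is unaffected. If practice is already planned, state it there.

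Sections 2.3.1 and 2.3.3 differ on whether the loads are chosen in a session 1–2 h before data collection or on a separate day. These must be reconciled, and the timing of the practice trials set with them.

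State the order of the two modalities. If it is not yet fixed by other constraints, randomise or counterbalance it and include a period term, so that remaining practice gain does not fall on one modality.

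The practice trials cost about 5–10 minutes per participant in a session already planned, with no new equipment or staff and slight extra exertion. They reduce the practice effect without removing it, so within-condition changes still need cautious reading. They do nothing about the stretching between the baseline and post-fatigue mobility tests.
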